### Objective

This trial aims to validate the use of *SDC2* methylation in stool DNA for early detection of CRC in asymptomatic populations. The primary endpoint of this study is to evaluate the sensitivity and specificity of the EarlyTect™-Colon Cancer for detecting CRC.

### Sample size calculation

Because this is not a randomized controlled trial, a statistical calculation for comparative analysis was not considered. Instead, we have assumed that the prevalence of colon polyps in Korea is 25% based on our previous pilot study, in which we found an 80% sensitivity of EarlyTect™-Colon Cancer for detecting CRC and polyps in 585 patients [19]. Therefore, at least 476 participants are needed to identify polyps or cancers. In our previous study, we intentionally controlled the types of cases (i.e., 245 CRC, 44 adenomatous polyps, and 245 negative colonoscopy results). However, we will enroll more than two times the number of cases (n = 1000) in this trial and specifically include asymptomatic participants who will undergo colonoscopy. Assuming a drop-out rate of 10%, 1112 participants will be enrolled in this trial.

### Data collection and management

The authors will use an electronic CRF (Excel, Microsoft, USA) to record clinical data and information. Principal investigators or clinical research coordinators at each site will enter clinical data into the CRF. Approved researchers from the central data managing institution will manage the data and information. Only the principal investigator will be able to access the final trial dataset and analyze it. Personal information regarding the enrolled participants will remain anonymous for 5 years and deleted to protect confidentiality.

### Drop-out

A participant can be removed from the trial for the following reasons:Submission of an unacceptable stool sampleRefusal to participate for any reason

### Statistical analysis

To calculate sensitivity and specificity, the test results will be denoted with dichotomous variables, namely “1” for methylation-positive individuals and “0” for methylation-negative individuals. Sensitivity and specificity for CRC detection, area under the curve (AUC) value, and 95% confidence interval (CI) will be calculated using receiver operating characteristics (ROC) analysis (SAS v.9.4). The cut-off value for C_T_ will be less than 40, and the following endpoints will be assessed:True positive (TP): *SDC2* methylation-positive in CRC patientsTrue negative (TN): *SDC2* methylation-negative in the control (negative) subjectsFalse-positive (FP): *SDC2* methylation-positive in the control subjectsFalse-negative (FN): *SDC2* methylation-negative in CRC patientsSensitivity = 100 × TP/(TP + FN)Specificity = 100 × TN/(TN + FP)Negative predictive value (NPV) = TN/(TN + FN)Positive predictive value (PPV) = TP/(TP + FP)

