## Methods/design

### Study design

This study is a prospective, multicenter trial to evaluate the clinical performance of a device (EarlyTect™-Colon Cancer, Genomictree, Daejeon, Korea) that allows for the quantitative detection of a single DNA marker, *SDC2* methylation, in human stool DNA from asymptomatic individuals.

Before the study is initiated, the staff will be trained in all aspects of the study, including the assay procedure and instrument use. All eligible participants scheduled for colonoscopy for any reason will be enrolled in this trial. Before initiating bowel preparation for colonoscopy, all participants will collect at least 20 g of their stool using a plastic collection tube (50 mL) that is included in the kit. The following samples will be considered inappropriate for analysis and excluded: diarrhea or loose stool, quantities less than 20 g, samples collected during bowel preparation, and samples submitted over 2 weeks after collection. Samples collected by the participant for the EarlyTect™-Colon Cancer test will be sent to a central laboratory.

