**Fig. 1 Fig1:**
[figure not shown]
Schematic diagram of the workflow of the trial

The *SDC2* methylation test will be performed according to the GT-CRC-UM-701 protocol (provided by the Sponsor) using the AB 7500 Fast Real-time PCR System (Thermo Fisher Scientific, Waltham, MA, USA). Briefly, 2 µg stool-derived genomic DNA will be chemically modified with sodium bisulfite using the EZ DNA Methylation-Gold kit (ZYMO Research, USA), according to the manufacturer’s instructions. For PCR analysis, *SDC2* and *COL2A1* control reactions will be performed twice in a single tube, as previously described [18, 19]. C_T_ values will be calculated using the software accompanying the AB 7500 Fast Real-Time PCR System. *SDC2* methylation will be considered detected if C_T_ is less than 40 cycles and not detected if C_T_ is not measurable [17]. To maximize clinical sensitivity, *SDC2* methylation will be considered positive if at least one of two PCR reactions has detectable methylated *SDC2*. Thus, samples will be categorized as positive if at least one of two reactions (1/2 algorithm) has detectable *SDC2* and considered negative if *SDC2* methylation is not measurable in both reactions. Our previous clinical study showed that the 95% limit of detection of the EarlyTect™-Colon Cancer assay was 34.5 pg, corresponding to approximately 20 diploid genome copies [19]. Reproducibility and repeatability of the assay were acceptable, within a coefficient of variation of 5%. A total of 23 potential interfering substances, selected because of their clinical and dietary uses in South Korea, were confirmed to have no effect on the test performance of EarlyTect™-Colon Cancer assay. The assay also exhibited no cross-reactivity, even when excess amounts (10^5^–10^6^ genome copies) of bacterial and viral DNA were tested.

Results from the EarlyTect™-Colon Cancer test will be compared against those obtained by colonoscopy and any corresponding diagnostic histopathology from clinically significant biopsied or subsequently excised lesions. Based on these results, participants will be divided into three groups: CRC (group 1), polyp (group 2), and negative (control). The following clinical data will be recorded for the participants: sex, age, colonoscopy results, and clinical stage (in the CRC case group).

Participant selection criteria are as follows:

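### PPV and NPV for CRC leave out the polyp group, so PPV as defined is too high whenever any polyp participant tests positive, and it does not describe the cohort tested

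*Protocol article*

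**What the plan says.** The Statistical analysis section defines four cells. True positives and false negatives are counted in CRC patients; true negatives and false positives are counted in the control (negative) subjects. From these cells it forms "Positive predictive value (PPV) = TP/(TP + FP" and "Negative predictive value (NPV) = TN/(TN + FN".

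The Study design section (text after Fig. 1) says that "participants will be divided into three groups: CRC (group 1), polyp (group 2), and negative (control". Polyp is thus a group of its own and is not part of the controls.

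Recruitment is by cohort: "All eligible participants scheduled for colonoscopy for any reason will be enrolled in this trial". The Sample size calculation section says "we have assumed that the prevalence of colon polyps in Korea is 25% based on our previous pilot study".

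The Objective section names sensitivity and specificity for CRC as the primary endpoint. The document gives no numerical PPV for this trial, no CRC prevalence in the cohort, and no separate test-positivity rate for polyps.

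**The concern.** A predictive value is conditional on the test result: of everyone who tests positive, what share has CRC? Under the written definitions, a participant with a positive stool test, a polyp and no cancer is in none of the four cells. That person is left out of the PPV denominator although the test was positive and no cancer was found.

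The Sample size calculation section contrasts this trial with an earlier study whose case mix was set by design, and the Discussion calls that study case-controlled. Enrolling a cohort is what makes predictive values estimable; dropping the middle group brings back a contrast of cases against clean colons.

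At stake is the number of positive tests per cancer found. The article hopes that the test can make colonoscopy selective, and PPV is the figure that bears on this most directly. The Background says that methylation of certain genes may occur in adenomatous polyps, and the Discussion reports that *SDC2* methylation is frequent in early neoplasia. Some positives among polyp participants are therefore to be expected.

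**Working it through.** **No stated PPV to reproduce.** The article gives formulas only. Its planned evaluable number (1000, inflated for 10% drop-out: 1000/0.9 = 1111.1, rounded up to the stated 1112) serves as the base.

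**Direction, without assumptions.** Let P+ and P− be the polyp participants who test positive and negative.

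- PPV as defined = TP/(TP + FP); whole cohort = TP/(TP + FP + P+). Their ratio is 1 + P+/(TP + FP), which exceeds 1 whenever P+ > 0.
- NPV as defined = TN/(TN + FN); whole cohort = (TN + P−)/(TN + P− + FN), which is equal or higher. NPV as defined is, if anything, slightly too low.

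**Inputs for the illustration.**

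- Polyps 25%: the article's assumed prevalence in Korea, applied here to the cohort.
- Sensitivity and control specificity 90%: assumed. The Background reports more than 90% for each in earlier work.
- CRC prevalence 1%: assumed; not in the document.
- Polyp positivity q of 10%, 24%, 40% or 60%: assumed; not in the document. At 10%, polyps test positive only as often as controls.

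Per 1000 participants there are 10 CRC, 250 polyp and 740 control. TP = 9, FN = 1, FP = 74, TN = 666. PPV as defined = 9/83 = 10.8%; NPV as defined = 666/667 = 99.85%.

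| q | P+ | Whole-cohort PPV | Ratio | Whole-cohort NPV |
|---|---|---|---|---|
| 10% | 25 | 9/108 = 8.3% | 108/83 = 1.30 | 891/892 = 99.89% |
| 24% | 60 | 9/143 = 6.3% | 143/83 = 1.72 | 856/857 = 99.88% |
| 40% | 100 | 9/183 = 4.9% | 183/83 = 2.20 | 816/817 = 99.88% |
| 60% | 150 | 9/233 = 3.9% | 233/83 = 2.81 | 766/767 = 99.87% |

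**Where 24% comes from, and how weak it is.** The article says "we found an 80% sensitivity of EarlyTect™-Colon Cancer for detecting CRC and polyps in 585 patients" and gives the case mix as "245 CRC, 44 adenomatous polyps, and 245 negative colonoscopy results". If CRC sensitivity was 90%, then (0.80 × 289 − 0.90 × 245)/44 = 10.7/44 = 24%. At 94% it becomes 0.9/44 = 2%. The listed groups sum to 534, not 585; if the other 51 were polyps, the 90% case gives (0.80 × 340 − 220.5)/95 = 54%. The pilot figures therefore do not fix q.

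**Sensitivity to the inputs.**

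- CRC prevalence 0.5% (5 CRC, 745 controls): 4.5/79 = 5.7% as defined, against 4.3%, 3.2%, 2.5% or 2.0%.
- CRC prevalence 5%, specificity 98%, q = 2%: 76.3% against 70.3%, ratio 1.08.
- CRC prevalence 1%, specificity 98%, q = 40%: 37.8% against 7.3%, ratio 5.2.

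**The same cells feed specificity.** In the 1% scenario, 90% in controls becomes (666 + 200)/990 = 87.5% over all non-CRC participants at q = 20%, and (666 + 125)/990 = 79.9% at q = 50%.

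**The case against.** The formulas are the textbook ones, and a contrast of CRC with clean colons is a legitimate declared choice for specificity. A polyp found after a positive test can also be a useful finding rather than a plain error. Results stay recorded by group, so a whole-cohort PPV remains computable. PPV and NPV are not the primary endpoint.

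Much of this stands, and it lowers the weight of the point. It does not rescue the definition. True positives are CRC only, so this is a PPV for CRC, and its denominator has to hold every positive test. The value of finding polyps is better shown by reporting their share of the positives than by leaving them out. Nor is this a detail left to an analysis plan, because the cells are written out.

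Stronger readings are tempting but unsupported:

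- *That the overstatement has a known size.* It depends on CRC prevalence and polyp positivity, neither of which is given, and the 25% is a national assumption for a cohort that is older or high-risk.
- *That the article reports a wrong PPV for this trial.* It gives a formula, not a value.
- *That NPV is inflated.* It moves slightly the other way.
- *That the repaired PPV would describe average-risk screening.* Entry requires age 60 or over or high-risk criteria, and the Discussion leaves average-risk people to a later study.
- *That stool results send participants to colonoscopy here.* All are already scheduled, and the results are disclosed after enrolment ends.

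**Conclusion.** The point holds. As written, polyp participants enter neither predictive value, so PPV for CRC is too high whenever any of them tests positive, and it does not describe the cohort tested. This direction needs no assumption about size.

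With CRC prevalence 1%, sensitivity and control specificity 90%, and polyps 25%, the overstatement is about 1.3 to 2.8 times for polyp positivity of 10% to 60%. Put the other way, the whole-cohort PPV is 23% to 64% lower than the defined one. Other inputs give less or much more. NPV changes by less than 0.05 percentage points in these four scenarios.

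Because the primary endpoint is sensitivity and specificity, and the data needed for a correct PPV are collected anyway, this is a should-fix point.

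**What to change.** In the Statistical analysis section:

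1. Define PPV for CRC as CRC test-positives divided by all test-positives (CRC, polyp and control).
2. Define NPV for CRC as all non-CRC test-negatives (polyp plus control) divided by all test-negatives.
3. Report test-positives split into CRC, polyp and negative colonoscopy.
4. State explicitly that any specificity computed in controls only uses a different denominator from these predictive values, so that false positive does not carry two meanings in one section.
5. Say that the predictive values apply to this cohort (aged 60 or over, or high-risk), not to average-risk screening.

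The cost is rewording and one extra table row or two; no new data are needed. The reported PPV will be less favourable. At submission 231 patients had been enrolled and methylation results were to stay undisclosed until enrolment was complete, so at that date the change could still be made before results were known.

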### Safety evaluation and reporting of adverse effects

We anticipate no adverse events related to using the device in this trial.

### Data monitoring

A committee will be organized for trial supervision. All members of the committee will be certified according to Good Clinical Practices at each institution. The committee will monitor all processes, including data collection, records, and management, as well as advise and request the principal investigator to alter plans if needed.

### Protocol modification

If necessary, the protocol can be modified following agreement between the principal investigator and trial participants.

## Discussion

Using cancer-specific methylated DNA as a target for the early detection of cancer has several advantages, when compared with using known biomarkers [15]. (1) Unlike mRNA or protein, DNA is not easily degraded outside the body and maintains relatively high stability when isolated from body fluids for non-invasive diagnosis. (2) DNA can be amplified by PCR, which enables effective detection of minute quantities of methylated biomarker DNA in patient samples. (3) mRNA and protein markers require multiplexing to increase their accuracy in cancer diagnosis, whereas methylated biomarkers can diagnose cancer with a single gene and are not greatly affected by sample purity. (4) Biomarker levels can vary based on changes in emotional, physiological, or pathological factors that are unrelated to cancer; however, DNA methylation is highly robust in terms of detection because no such changes have been reported in vivo. (5) DNA methylation has a higher specificity for specific cancers than gene mutations, mRNA, or protein markers. (6) Unlike with other markers, early detection is possible with DNA methylation because methylation occurs in pre-cancerous lesions or early cancers.

Despite its accuracy, patients who undergo colonoscopy feel discomfort due to its invasiveness and the need for extensive bowel preparation. Therefore, a non-invasive and accurate novel screening technique can help make colonoscopy a selective procedure. As mentioned above, we previously demonstrated the diagnostic accuracy of the EarlyTect™-Colon Cancer test for detecting CRC in a case-controlled study [19]. EarlyTect™-Colon Cancer test exhibited high analytical sensitivity and specificity for *SDC2* methylation detection, as well as high reproducibility [19]. These results provided strong evidence that EarlyTect™-Colon Cancer test is optimized for analyzing stool-derived DNA. To further improve clinical sensitivity for detecting precancerous lesions, digital PCR or next generation sequencing techniques will be helpful to detect *SDC2* methylation in stool samples.

Our stool DNA-based test employs a single methylation marker *SDC2* for detecting CRC, whereas the multitarget stool-based DNA test called Cologuard (which is USA Food and Drug Administration-approved) assesses the presence of 2 methylation markers (*BMP3* and *NDRG4*) and *KRAS* mutations and includes FIT of stool samples. The *SDC2* methylation test has the same high sensitivity for detecting CRC as Cologuard [20]. Furthermore, the NPV of our test is comparable to that of Cologuard (99.9%) and FIT (99.7%), indicating that a negative methylation test result can provide similar information regarding the absence of CRC [18].

It has been reported that aberrant *SDC2* methylation occurs frequently in the early stages of neoplasia, is maintained in advanced CRC, and is unaffected by such factors as disease stage, age, sex, and race. These findings were observed in clinical studies comparing methylation of *SDC2* in stool DNA from patients with different stages of CRC, as well as from healthy subjects [17–19, 21, 22]. Several other studies have also reported tests for detecting CRC based on *SDC2* methylation in stool DNA [6, 21, 22]. Overall, these reports showed sensitivities of 77.4–81.1% and specificities of 88.2–98%, which are comparable to the values of our test.

Nevertheless, trials involving asymptomatic individuals are required to confirm whether the EarlyTect™-Colon Cancer device is a useful cancer-screening tool. Enrollment for this trial began on June 7, 2020 after registration was opened on ClinicalTrials.gov on March 11, 2020 (NCT04304131). This is the first prospective, multicenter trial to evaluate the clinical performance of EarlyTect™-Colon Cancer test in asymptomatic high-risk Korean populations. This test uses a real-time PCR assay to detect a single novel DNA methylation marker, methylated *SDC2*, in stool DNA. We were the first group to identify the usefulness of this biomarker, and we proprietarily developed the EarlyTect™-Colon Cancer test for early CRC detection. Some similar clinical trials have taken advantage of our discovery and used methylated *SDC2* as a biomarker in stool DNA tests for CRC detection; these tests exhibited very good performance, as expected. These similar trials utilizing methylated *SDC2* as a biomarker provide further evidence that *SDC2* methylation analysis is a useful noninvasive diagnostic approach for early detection of CRC, which may improve current diagnostic practices when used in conjunction with existing screening tools, such as FIT and colonoscopy [6, 21, 22].

We expect that this trial will provide results that will be beneficial for healthy people who want to avoid colonoscopy. Although the EarlyTect™-Colon Cancer test cannot match colonoscopy in terms of accuracy, it can still be used for early detection of CRC. This study protocol uses a prospective clinical study design to validate the effectiveness of *SDC2* methylation, a new biomarker for non-invasive early detection of CRC, in a relatively small population of high-risk individuals. This work should provide practical information for the design of a larger-scale prospective clinical study of an average-risk population to clarify the use of EarlyTect™-Colon Cancer test as a screening tool for CRC.

### Study status

A total of 231 patients were enrolled at the time of submission (November 2, 2020).

## Data Availability

Not applicable.

## Abbreviations

CRC: Colorectal cancer
*SDC2*: Syndecan-2
CRF: Case report form
TP: True positive
TN: True negative
FP: False positive
FN: False negative
FIT: Fecal immunochemical test
CT: Computed tomography
